### Data analysis

#### Primary outcome - aim 1

Compare the effectiveness of two post-discharge models of care: 1) Quitline referral, and 2) multi-session telephone counseling.

Descriptive analysis techniques will be used to present baseline characteristics of participants in each treatment arm across the two centers and stratified by center. We will use tests of means and proportions to compare characteristics of the treatment groups and log-linear tests to investigate treatment by center interaction. If the differences between the centers are not significant, the subsequent comparison of the primary outcome will be performed between the two treatment groups across the centers, otherwise it will be stratified on center. Baseline characteristics of participants who drop out will be compared with the other participants to examine whether the drop out is at random. In the case of differential dropout rates (for example, between treatment arms, between centers), we will further examine the factors that led to the drop out. The two-sided z-test of proportions will be used to compare the rates of abstinence from smoking at 6-month follow-up of the two treatment arms.

#### Primary outcome - aim 2

Cost-effectiveness analysis.

Following accepted standards for cost-effectiveness analysis in health care [23], we will perform analyses from a societal perspective (all expenditures, regardless of whether from payers, patients or other sources). We will also perform sensitivity analyses from a payer perspective, as this perspective is sometimes preferred by decision makers. Costs will be discounted at a rate of 3%. Outcomes will be expressed both in terms of cost per quality-adjusted life year (QALY) and cost per life year.

Data inputs will include differential quit rates, along with measures of their uncertainty. To estimate their impact, we will develop a Markov model that will predict differential incidence and impact of cardiovascular and pulmonary disease, based on observed differential quit rates of known duration, effect size, and statistical certitude. In base case analyses, we will conservatively assume that smoking cessation has no beneficial impact on quality of life apart from decreasing the likelihood of these longer-term adverse outcomes, although in sensitivity analyses we can consider various scenarios regarding this effect, including any changes in quality of life. We will also explore different assumptions about duration of intervention effect.

Cost inputs will include the costs of staff time for the in- and out-of-hospital components, including additional staff training required to carry out the intervention. Staff will prospectively track time trying to call each patient and the duration of each counseling call (to value the patient time-costs of participating). We will track pharmacy expenditures for smoking-cessation medications. We will use cigarette smoking frequency to estimate cost-savings to patients from decreased cigarette consumption. Finally, our analyses will include the potential for downstream cost-savings (reduced incidence of cardiovascular and pulmonary disease) and cost increase (additional medical care).

By comparing incremental costs to incremental benefits over a lifetime horizon, we will estimate the value of this intervention, enabling its value to be compared to alternative resource uses. In addition, we will compare incremental cost-effectiveness ratios to accepted standards for favorable value in the US ($100,000 per life-year, and/or $100,000 per QALY).

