### Randomization

We will randomize participants to one of the two arms of the trial in a 1:1 ratio shortly after discharge, when information regarding discharge location becomes available in the medical record. Participants who have enrolled in the study while they are in the hospital, but who are then discharged to a nursing home or other facility where smoking is forbidden and patients cannot leave to smoke, will be deemed ineligible and will not undergo randomization. Allocation concealment will be ensured, as the randomization code will not be released until the patients are recruited into the trial and all baseline measures are taken. We arranged our complete randomization scheme before the study began, given the expected number of participants from our power and sample size analysis. The randomization was performed using routines for random number generation available in R Package for Scientific Computing (http://www.r-project.org). To prevent a small number of patients in a particular study site from all receiving, by chance, the same treatment, treatment assignment was randomized with stratification on the study site (Bellevue versus Manhattan VA). Study staff who perform follow-up assessments are blinded to participants’ intervention assignment, as are those performing the analyses of saliva cotinine. The trial statistician performing the analyses of all study data is masked to the treatment allocation.

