### Sample size

We will compare the 6-month abstinence rates of the two arms of our trial. There are approximately 4,000 ‘current smokers’ admitted to Bellevue non-psychiatric services and 2,400 admitted to psychiatric services per year. We anticipate enrolling 20% of the non-psychiatric patients and 10% of the psychiatric patients – netting a total enrollment of 1,040 Bellevue patients per year of the study. At the VA, there are approximately 1,200 ‘current smokers’ admitted to non-psychiatric services and 500 admitted to psychiatric services per year. With a similar anticipated enrollment rate, our projected enrollment at the VA is 290 patients per year of the study.

In total, we expect to enroll a total of approximately 3,000 patients over the 2.5 years of enrollment, or 1,500 per arm. We expect that the long-term abstinence rate in the Quitline arm will be 5%. With 1,500 participants in each treatment arm, the two-sided unpooled z-test of proportions will have 80% power to detect 2.47% difference in abstinence rates between the two arms at the 0.05 significance level, meaning detecting an increase in cessation rate to 7.47%.

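### A preliminary significance test chooses between a pooled and a centre-stratified primary comparison; because site is already a randomisation stratum, one site-stratified analysis can be fixed in advance at no cost

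*Protocol article*

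**What the plan says.** Under aim 1 of the Data analysis section, the article plans "log-linear tests to investigate treatment by center interaction". A decision rule follows, which opens with "If the differences between the centers are not significant, the subsequent comparison of the primary outcome will be performed between the two treatment groups across". That sentence then closes by naming both branches: "primary outcome will be performed between the two treatment groups across the centers, otherwise it will be stratified on center". The same paragraph names the primary test: "The two-sided z-test of proportions will be used to compare the rates of abstinence from smoking at 6-month follow-up". No site term is attached to it.

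The Randomization section says "treatment assignment was randomized with stratification on the study site (Bellevue versus Manhattan VA"), and "We will randomize participants to one of the two arms of the trial in a 1:1 ratio".

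The Sample size section plans for a single overall comparison: "the two-sided unpooled z-test of proportions will have 80% power to detect 2.47% difference in abstinence rates between the two arms". The test is to be run "at the 0.05 significance level, meaning detecting an increase in cessation rate to 7.47" per cent.

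**The concern.** The analysis that matches the randomisation is used only if a test on the trial's own data turns out significant, so the primary analysis is not fixed in advance. Three elements are open:

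- **The quantity tested.** It could be the treatment-by-centre interaction just mentioned, the baseline characteristics discussed in the same paragraph, or the abstinence rates. The Setting section describes very different inpatient populations (17% Caucasian at Bellevue, about 60% at the VA), so a test of baseline differences would probably be significant.
- **The level of the preliminary test.** None is given.
- **The meaning of the stratified branch.** It could be one test combined over sites or separate results for each site. The same paragraph uses the expression for baseline tables, where it means separate presentation. The Randomization section uses stratification in its ordinary design sense.

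At stake is whether the trial ends with one confirmatory answer at the 0.05 level or, in some data sets, with two smaller answers and no stated rule for combining them.

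**Working it through.** **Inputs from the Sample size section.** Control rate p1 = 0.05, alternative p2 = 0.0747, 1,500 per arm, two-sided 0.05. Projected enrolment per year is 1,040 (Bellevue) and 290 (VA). The Bellevue share is 1,040 / 1,330 = 0.782, so 1,500 per arm divides into 1,173 and 327.

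**Assumptions not in the article.** Preliminary test at 0.05; the site abstinence rates shown below; site sizes scaled by the enrolment ratio (1,330 × 2.5 = 3,325, against the stated approximate total of 3,000).

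**Step 1: the plan's own figure.** Power = Φ(d / √[(p1q1 + p2q2)/n] − 1.96).
- p1q1 + p2q2 = 0.0475 + 0.06912 = 0.11662
- n = 1,500: SE = 0.00882; 0.0247 / 0.00882 = 2.80; power = Φ(0.84) = 0.800

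The stated 80% reproduces.

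**Step 2: the same formula within one centre.**
- Bellevue, n = 1,173: SE = 0.00997; 0.0247 / 0.00997 = 2.48; power = Φ(0.52) = 0.70
- VA, n = 327: SE = 0.01888; 0.0247 / 0.01888 = 1.31; power = Φ(−0.65) = 0.26

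**Step 3: type I error of the rule.** Simulation with 1,000,000 trials per scenario. The interaction pre-test is a Wald test on the difference of the two centres' log odds ratios. The combined stratified test is Cochran-Mantel-Haenszel (CMH). In the split reading, an unadjusted win in either centre counts.

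| No treatment effect; site rates | Always pooled | Always CMH | Interaction pre-test, then CMH | Interaction pre-test, then split | Centre-rate pre-test, then split |
|---|---|---|---|---|---|
| 5% / 5% | 0.050 | 0.050 | 0.050 | 0.081 | 0.053 |
| 4.5% / 6.8% | 0.050 | 0.050 | 0.050 | 0.081 | 0.078 |
| 4.0% / 8.6% | 0.049 | 0.050 | 0.049 | 0.079 | 0.098 |

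The 0.081 in the first row breaks down as follows. The interaction is significant in 0.0447 of null trials, and within those at least one centre is significant in 0.743. The split branch contributes 0.0447 × 0.743 = 0.033, and the pooled branch the remaining 0.048. For reference, two independent unadjusted tests give 1 − 0.95² = 0.0975.

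**Step 4: how often the branch is entered when there is an effect.** With 5% versus 7.47% at both centres, the interaction is significant in 4.6% of trials. If the effect exists only at Bellevue, it is significant in 18.5%, so the pre-test is a weak detector of a real centre difference.

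**Step 5: cost of a fixed stratified test.** With 5% versus 7.47% at both sites, power is 0.800 for CMH and 0.800 pooled. The near-identity is expected. With 1:1 allocation within site the Mantel-Haenszel weight is m·m/(2m) = m/2, so the stratified risk difference is (1,173·dB + 327·dV)/1,500, which is the crude difference. Only the standard error changes, and only slightly. Pooled and CMH decisions differed in at most about 0.1% of trials.

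**The case against.** The strongest reply is that a stratified comparison ordinarily means one combined test. On that reading the two-step rule keeps its size at about 0.050, and pooled and stratified tests almost never disagree. That stands: any inflation is conditional on the split reading.

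A reader might infer that the trial runs at 8% type I error. The article does not support that. The figure needs three things it does not state: separate centre tests, an unadjusted win in either centre counted as success, and an outcome-interaction pre-test at 0.05. If both centres had to be significant, size would be about 0.049.

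A reader might also infer that power falls from 80% to 70% or 26%. Those are powers inside a branch entered in about 4.5% of trials under a common effect. Overall two-step power stays near 80%: 0.800 with a combined test, 0.809 with either centre, and about 0.77 if both are required.

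Nor does ignoring the stratum in the pooled branch cause measurable damage here; Step 5 shows why.

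The preliminary test may also concern baseline characteristics rather than outcomes, in which case the interaction simulation does not apply. The trial statistician is masked to allocation, which limits bias in choosing a branch.

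Finally, the level of a pre-test and the exact stratified statistic are details that an article may leave to an analysis plan. The conditional rule itself is different: the article states it for the primary outcome, and an analysis plan could remove it only by overriding this text. None of these points gives the rule a function.

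**Conclusion.** The point holds in a limited form. The article makes the primary 6-month comparison depend on a preliminary significance test whose quantity and level are not fixed, although site is a randomisation stratum. The numerical consequence ranges from practically nothing (size about 0.050, one combined test) to a type I error of about 0.08 (separate unadjusted centre tests, either counted, interaction pre-test at an assumed 0.05). With a pre-test on centre abstinence rates, the split reading gives 0.053 to 0.098 over the assumed site rates. The text does not say which reading applies. Under one the rule inflates error, and under the other it has no purpose, so neither is a reason to keep it. Because the harm is conditional and the remedy costs nothing, this is a free improvement and not a flaw that invalidates the planned test.

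**What to change.** Delete the conditional sentence. State that the primary comparison of 6-month abstinence will be stratified by site (Bellevue, Manhattan VA) in all cases, whatever any test of centre differences shows; a Mantel-Haenszel risk difference with its z-test at the two-sided 0.05 level would serve. Report the treatment-by-centre interaction and centre-specific estimates with confidence intervals as supportive only. The Secondary outcomes section already plans to examine interaction with hospital, so nothing is lost.

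The cost is one paragraph of wording: no new data, no extra patients, and power unchanged at about 80%. The article reports that enrolment was still under way at submission, so the change could be made before outcome data are examined.

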### Outcome measures

Our primary outcome will be 30-day point-prevalence abstinence from smoking, as measured at 6-month follow-up post-discharge via participant self-report. We will perform this assessment via telephone survey. Our hypotheses are that, compared to control (Quitline), multisession phone counseling patients will have higher rates of smoking cessation, lower cigarette consumption, and more quit attempts.

Secondary outcomes are biochemically validated abstinence from smoking at 6-month follow-up (as measured by salivary cotinine mailed in for collection via a protocol described more fully elsewhere [19]) and smoking abstinence at 12-month post-discharge follow-up (as measured by participant self-report on telephone survey). For pre-specified subgroup analyses, we will compare outcomes by participant race/ethnicity, immigrant status, inpatient diagnosis, and location of hospitalization.

As an exploratory sub-study, we will examine patient use of text messaging and interest in a cessation intervention using this technology. Given the mobility and relative youth of our population, text messaging could be an effective way to reach these patients. The aims of this exploratory study are to assess: 1) the prevalence of regular text messaging use, and 2) interest in counseling delivered via text messaging.

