### Co-variables of interest

Covariables of interest are found in Table 2. Among these variables will be sociodemographic measures; measures of nicotine addiction, smoking cessation history, and interest in quitting; comorbid mood symptoms and substance use history, and medical history. We will also collect information about the index hospitalization, including length of stay, principal diagnoses, and procedure codes.

**Table 2 T2:** Data collection items and schedule

**Measure**	**Baseline**	**2-Month follow-up**	**4-Month follow-up**	**6-Month follow-up**	**9-Month follow-up**	**12-Month follow-up**

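### The primary z-test is valid but unadjusted: it uses none of the baseline predictors collected, and uses site only if a preliminary test is significant, which gives up a little power

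*Protocol article*

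**What the plan says.** The endpoint is binary. Under Outcome measures: "Our primary outcome will be 30-day point-prevalence abstinence from smoking, as measured at 6-month follow-up post-discharge via participant self-report". Under Data analysis, aim 1, the test is named: "The two-sided z-test of proportions will be used to compare the rates of abstinence from smoking at 6-month follow-up of the two treatment arms". The Sample size section is built on the same test in its unpooled form.

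The only step beyond a crude comparison concerns center, and it is conditional. The plan first runs log-linear tests for treatment-by-center interaction. Where no significant center difference is found, the arms are compared with both hospitals pooled. For the opposite case the plan says of the comparison: "otherwise it will be stratified on center". Site was the randomization stratum (Randomization): "treatment assignment was randomized with stratification on the study site (Bellevue versus Manhattan VA"). No other stratification factor is named.

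The Co-variables of interest section lists, among other things, "measures of nicotine addiction, smoking cessation history, and interest in quitting", together with mood symptoms, substance use and details of the index admission. Table 2 schedules the smoking, mood and substance use measures at baseline. For comparing the arms at baseline, Data analysis says: "We will use tests of means and proportions to compare characteristics of the treatment groups". No adjustment follows from the result of those tests.

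**The concern.** Three features of the plan fit together poorly.

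1. The trial collects variables that plausibly predict 6-month abstinence and calls them covariables, but the primary comparison leaves them out. A prespecified adjusted analysis of the same patients would have a slightly smaller standard error if those variables predict the outcome.
2. The arms are tested against each other at baseline. In a randomized trial such a test asks only whether chance produced a difference. Nothing in the plan uses the answer, so the tests do not improve the estimate.
3. Site was built into the randomization, yet it enters the primary comparison only through a preliminary significance test. The form of the primary analysis therefore depends on the data.

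At stake are a small amount of power and a single, fixed definition of the primary analysis. The design has 80% power at full enrollment.

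**Working it through.** **Inputs.** From Sample size: n = 1,500 per arm, control rate p1 = 0.05, target p2 = 0.0747, two-sided alpha 0.05, unpooled z-test, stated power 80%. From Randomization: "We will randomize participants to one of the two arms of the trial in a 1:1 ratio shortly after discharge". R², the share of outcome variance explained by baseline covariates, is not in the article. It is an assumption and is shown as a range.

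**Step 1: reproduce the stated power.**

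SE = √[(0.05×0.95 + 0.0747×0.9253)/1,500] = √(0.11662/1,500) = 0.008817.

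Power = Φ(0.0247/0.008817 − 1.960) = Φ(2.801 − 1.960) = Φ(0.841) = 79.99%.

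The required n is 1,500.3 per arm and the detectable difference is 2.470 points. The plan's figure reproduces.

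**Step 2: power with adjustment.** In a 1:1 trial, adjustment scales the variance by about (1 − R²), so power = Φ(2.801/√(1 − R²) − 1.960). The patients saved per arm are 1,500 × R².

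| Assumed R² | Power | Equivalent patients per arm |
|---|---|---|
| 0 | 80.0% | 0 |
| 0.01 | 80.4% | 15 |
| 0.02 | 80.8% | 30 |
| 0.035 | 81.4% | 52 |
| 0.05 | 82.0% | 75 |
| 0.067 | 82.6% | 100 |
| 0.10 | 84.0% | 150 |

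**Step 3: what these R² values mean.** At such low abstinence rates even a good predictor explains little variance. A simulation used one normally distributed prognostic score, logistic regression with standardization to a risk difference, and 1,500 trials per setting (Monte Carlo error about 1 point of power):

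| c-statistic of score | R² | SE ratio, adjusted/crude | Power, crude → adjusted |
|---|---|---|---|
| 0.64 | 0.015 | 0.992 | 79.1% → 80.3% |
| 0.70 | 0.036 | 0.983 | 79.4% → 81.4% |
| 0.75 | 0.067 | 0.973 | 78.8% → 80.9% |
| 0.80 | 0.105 | 0.961 | 80.3% → 84.7% |

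The gain is about 1 to 3 points of power for c-statistics of 0.64 to 0.75. About 4 points needs a very strong score.

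**Step 4: chance imbalance.** The part of the crude difference due to imbalance on the score has standard deviation SE × √R². In 95% of trials the shift lies within ±1.96 × 0.008817 × √0.036 = ±0.33 points at R² = 0.036, and within ±0.56 points at R² = 0.105. The target difference is 2.47 points. The crude standard error already contains this variation.

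**Step 5: site alone.** Projected enrollment is 1,040 a year at Bellevue and 290 at the VA, so the VA share is w = 290/1,330 = 0.218. With site rates a and b and overall rate p, R² = w(1 − w)(a − b)²/[p(1 − p)]. Assumed rates of 5% and 10% give R² = 0.007; 4% and 12% give 0.020. Site should be in the model because it was a stratum and the analysis should be fixed, not because it adds much precision.

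**The case against.** The strongest reply is that nothing here is wrong. A two-sided z-test of proportions is valid in a 1:1 randomized trial, and it is the test on which the sample size was calculated. That stands in full.

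Several stronger readings are tempting, and the article does not support them:

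- **That the covariates are strong predictors.** The article gives no prognostic strength. They are plausible predictors, and at R² near 0.01 the gain is close to nil.
- **That the crude estimate is biased or unprotected against imbalance.** It is not. Its standard error and type I error already allow for chance imbalance, which is small at this sample size. Adjustment takes that imbalance out of the estimate; it does not repair an invalid test.
- **That baseline data serve only for description and between-arm tests.** Data analysis also compares dropouts with other participants on baseline characteristics. The Secondary outcomes section examines interactions with hospital, inpatient diagnosis and other characteristics.
- **That patients who have already quit show baseline spread.** That remark is in the description of the first counseling call, after randomization and in one arm. Entry requires smoking within the previous 30 days.
- **That adjustment is free.** It costs little, but covariates must be chosen and missing baseline values handled.

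It can also be said that adjusted models are usually left to an analysis plan, which is not shown. This carries less weight here. The article does not leave the primary method open: it names the unadjusted test and the conditional rule for center.

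**Conclusion.** The point holds as a minor missed efficiency. The primary comparison makes no use of plausible baseline predictors already scheduled for collection, and it makes the use of the randomization stratum depend on a preliminary test. For an assumed R² of 0.01 to 0.067, prespecified adjustment would raise power by about 0.4 to 2.6 points from 80.0%; 84% needs R² = 0.10. These figures assume the plan's 5% and 7.47%, 1,500 analyzed per arm, and a prognostic strength that the article does not state. The validity of the planned test and the sample size calculation are not in question.

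**What to change.** Before unmasking, name one primary analysis: a logistic regression of 6-month abstinence on arm, site and a short fixed list of baseline covariates. Examples are nicotine dependence or cigarettes per day, interest in quitting, and psychiatric versus non-psychiatric admission. Include site in every case, with no preliminary test. Report the standardized risk difference with its confidence interval, which keeps the scale used in Sample size. Keep the z-test as a supportive analysis. Describe baseline characteristics by arm, and drop the significance tests between arms on them.

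The planned rates imply about 1,500 × 0.05 + 1,500 × 0.0747 = 75 + 112 = 187 abstainers, enough for a model of this size. The cost is wording: the covariates and their coding must be named in advance, with a simple rule for the few missing baseline values. No new data and no change to sample size are needed, and the Randomization section says that the trial statistician is masked to allocation.

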##### C2. Telephone counseling arm

Patients in the Telephone Counseling arm will receive telephone calls from study staff at days and times convenient for the patient. To establish the first post-discharge contact, staff will call each patient up to 10 times during the 2 weeks following discharge. Once contact has been made, the staff will complete tailored, multi-session telephone counseling with the patients.

Our telephone counseling system includes proactive counseling, a structured protocol, and relapse-sensitive scheduling [22]. The content is based on Motivational Interviewing and Problem Solving Therapy and addresses behavioral and cognitive issues, including motivation, self-efficacy, difficult situations, comorbid symptoms, coping strategies, medication usage, and relapse prevention. The program staff members use a structured protocol to maintain a record of each of the counseling calls for internal quality assurance.

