### Intervention standardization and fidelity

The Quitline has a standardized protocol and has well-trained counselors answering its telephone calls and providing counseling. For the Telephone Counseling arm, the telephone counselors will undergo an intensive initial training consisting of a) 5 hours of Motivational Interviewing training with a clinical psychologist specializing in health psychology, and b) 20 to 30 hours of training on the study’s clinical protocols. This training will include role-plays with each other and with the study’s counselor supervisor. After the counselor supervisor has determined that a counselor has met the role-play training objectives, the counselor will advance to complete a series of standardized patient (SP) encounters. SP encounters will involve calling an actor trained to portray a smoker enrolled in the study and completing planning and follow-up counseling sessions per study protocol. The SP encounters will be audiotaped and reviewed by a clinical psychologist and the study’s counselor supervisor for adherence to trial protocols. Each counselor will complete two to four SP encounters, depending on their training needs as determined by the study’s counselor supervisor.

To ensure intervention standardization and fidelity after study implementation, a random sample of the counselors’ phone calls will be audiotaped and reviewed by a clinical psychologist and the study’s counselor supervisor. Feedback on the calls will be given to counselors verbally and documented using a standardized form with scales indicating whether the counselor adhered to Motivational Interviewing counseling techniques and met the appropriate clinical objectives. Counselors will also attend weekly group supervision meetings with a clinical psychologist, during which time the counselors’ active cases will be discussed with particular attention to difficult cases.

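### The primary z-test and its 80% power assume no variation between telephone counselors, so a claim about the counseling model beyond this trial's counselors needs a pre-specified sensitivity analysis

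*Protocol article*

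**What the plan says.** Under Data analysis (aim 1), the primary comparison between the arms at 6 months is fixed: "The two-sided z-test of proportions will be used to compare the rates of abstinence from smoking". The only structural refinement concerns center. If the centers do not differ significantly, the comparison "will be performed between the two treatment groups across the centers, otherwise it will be stratified on center".

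The Sample size section uses the same test, with 1,500 patients per arm and an expected Quitline abstinence rate of 5%: "the two-sided unpooled z-test of proportions will have 80% power to detect 2.47% difference in abstinence rates", at a two-sided 0.05 level. No design effect is mentioned.

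Randomization is 1:1 by patient, stratified by site only (Randomization). In the telephone arm, study staff deliver a planning session and then follow-up calls at six points after the quit date (C2, The planning session, Follow-up sessions). The section on standardization and fidelity says of the weekly group supervision that the counselors' "active cases will be discussed with particular attention to difficult cases". Section C2 adds: "The program staff members use a structured protocol to maintain a record of each of the counseling calls". In the Quitline arm an outside service gives one session of 15 to 20 minutes and a follow-up call (C1).

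Counselors appear in the article only in connection with delivery, training, fidelity and supervision. They do not enter the primary analysis or the sample size.

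**The concern.** When patients are randomized individually but one arm is treated by a limited number of therapists, outcomes in that arm can be correlated within therapist. This is a partially nested design: clustering in the telephone arm, and little or none in the Quitline arm, where contact is a single short session.

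The z-test uses the binomial variance in both arms. That variance leaves out any spread between counselors. The target difference is only 2.47 percentage points and caseloads would be large, so even a small ICC can matter.

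What is at stake is the reach of a positive result. Aim 1 compares two models of care, and the Discussion describes the interventions as generalizable to many kinds of institution. Such a conclusion extends to counselors who did not take part, so variation between counselors belongs in its error. The uncertainty of the quit rates also feeds the cost-effectiveness model.

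**Working it through.** **Inputs from the article.** Control rate p1 = 0.05; telephone rate p2 = 0.0747; n = 1,500 per arm; two-sided alpha 0.05; unpooled variance.

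**Inputs assumed.** The number of counselors k and the ICC are not given. The range used is k = 10 to 20 (m = 1,500/k = 150 to 75 patients each) and ICC = 0.001 to 0.005. It assumes equal caseloads and one counselor per patient.

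**Step 1: the plan's own figure.** Power = Φ(d / √(p1q1/n + p2q2/n) − 1.96), with d = 0.0247.
- p1q1 = 0.05 × 0.95 = 0.0475; p2q2 = 0.0747 × 0.9253 = 0.06912.
- Standard error = √((0.0475 + 0.06912)/1,500) = 0.008817.
- d/SE = 2.801, and Φ(2.801 − 1.96) = 80.0%.

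The stated 80% reproduces, and it does so with independent patients in both arms.

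**Step 2: clustering in the telephone arm only.**
- Design effect DE = 1 + (m − 1) × ICC.
- Type I error of the planned z-test for the broader target, at a common rate = 2 × (1 − Φ(1.96 × √(2/(1 + DE)))).
- Power with a correct SE = Φ(d / √(p1q1/n + DE × p2q2/n) − 1.96).
- The last column replaces 1.96 with a t critical value on Satterthwaite degrees of freedom (k − 1 for the telephone arm, 1,499 for the Quitline arm) and uses the noncentral t distribution.

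Example, k = 10 and ICC 0.005: DE = 1 + 149 × 0.005 = 1.745. Type I error = 2 × (1 − Φ(1.96 × √(2/2.745))) = 2 × (1 − Φ(1.673)) = 9.4%. SE = √((0.0475 + 1.745 × 0.06912)/1,500) = 0.01059, so power = Φ(2.333 − 1.96) = 65%.

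| Counselors | ICC | DE | Type I error, broader target | Power, correct SE | Power, small-sample df |
|---|---|---|---|---|---|
| any | 0 | 1.00 | 5.0% | 80% | 77% (k = 10), 79% (k = 20) |
| 20 | 0.001 | 1.07 | 5.4% | 78% | 77% |
| 20 | 0.005 | 1.37 | 7.2% | 72% | 70% |
| 10 | 0.001 | 1.15 | 5.9% | 77% | 73% |
| 10 | 0.005 | 1.75 | 9.4% | 65% | 60% |

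**Step 3: check by simulation.** Beta-binomial simulation of the planned z-test (40,000 runs per setting), with a true mean rate of 5% in both arms, rejected in 5.9% of runs (k = 10, ICC 0.001), 9.6% (k = 10, ICC 0.005) and 6.8% (k = 20, ICC 0.005). These agree with the formula.

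**Step 4: what the ICC means.** The between-counselor standard deviation around 7.47% is √(ICC × 0.06912). It is 0.8 points at ICC 0.001, 1.9 points at 0.005 and 2.6 points at 0.01.

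**The case against.** The case for leaving the plan alone is substantial, and much of it stands.

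- **Caseloads are inferred.** The article says that study staff make the calls and that patients may call program staff between sessions. Only the reference to active cases points to caseloads. Shared patients, or patients never reached, would dilute any clustering. This stands. The call records can settle it.
- **The z-test is not invalid.** A reader might infer that the binomial variance is right only if counselors do not differ at all. That is too strong. For inference about the counselors in this trial the test holds its level: a simulation with six fixed counselors whose rates ran from 2% to 8% around a mean of 5%, against 5% in the control arm, rejected in 4.9% of runs. It also holds under the null that counseling affects no patient. Inflation arises only for the wider target, when counselors differ yet average the Quitline rate.
- **The training rules do not show expected variation.** A reader might take the flexible number of standardized-patient encounters as an admission that counselors will differ in effect. Those encounters, the manual, the call audits and the weekly supervision are there to reduce differences.
- **Larger figures are strained.** Six counselors with ICC 0.01 would give 19% type I error and 43% power. That needs a between-counselor standard deviation of 2.6 points, more than the whole target difference of 2.47, despite common training.
- **Changing the primary test has a price.** With six counselors, a small-sample partially nested test has about 74% power even at ICC 0.
- **A sensitivity analysis may sit in an unseen analysis plan.** That is possible. But the primary test and its power are stated here without the assumption on which they rest.

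**Conclusion.** The point holds in conditional form. The 80% power is computed correctly, and the z-test is a legitimate primary analysis of an individually randomized trial. Both rest on an unstated assumption that counselors do not vary, and that assumption matters when the result is read as evidence about the counseling model in other hands.

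For that broader target, with 10 to 20 counselors and ICC 0.001 to 0.005, type I error is about 5.4% to 9.4%. Power with a correct standard error is about 78% to 65%, or about 77% to 60% with small-sample degrees of freedom. The low end is minor, and at ICC 0 the planned test is unaffected. The sizes depend on assumed inputs and on each patient having mainly one counselor, which the article does not confirm.

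The documents do not support concluding that the z-test must be replaced, or that patients must be assigned to counselors at randomization. The first is a trade-off against power. The second would change delivery in a trial that was already enrolling.

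**What to change.** - Keep the two-sided z-test as the primary analysis.
- Take the main counselor for each telephone-arm patient from the call records that are already kept. No assignment to counselors at randomization is needed.
- Pre-specify a partially nested sensitivity analysis of 6-month abstinence: a counselor random effect, or counselor-clustered standard errors with small-sample degrees of freedom, in the telephone arm only. Treat Quitline patients and never-reached telephone-arm patients as independent.
- Report the number of counselors and the counselor ICC.
- If a positive result does not hold in this analysis, qualify any general claim about the counseling model.
- State in the Sample size section that the 80% power assumes no counselor variation.

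Cost: one identifier drawn from existing records and one extra model, with no added patients or visits. If there are few counselors, the sensitivity interval will be wider and the ICC imprecise, so a failure to reach significance there should not by itself be read as evidence against the intervention.
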